### SPA therapy treatment

Each spa therapy session will comprise a mineral hydrojet session at 37 °C for 15 min, the thigh manipulated under mineral water at 38 °C by a physiotherapist for 10 min, manual massages, the application of mineral-matured mud at 45 °C to the knees for 15 min and supervised general mobilisation in a collective mineral water pool at 32 °C in groups of 8 patients for 15 min of 18 sessions, for 1 h each.

The main component of mineral waters are chlorobarbonated sodium in Royat (63) and Le Mont-Dore (63) spas centers and sodium chlorides in Bourbon Lancy (71).

Both groups will be mixed with the general public in the spa center. The spa therapist will not be aware of which patients will be taking part in the clinical trial.

The experimental and active comparator arms will receive unrestricted non-pharmacological, pharmacological and usual care during the study. Medication taken during or after the intervention will be reported in the follow-up questionnaires.

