#### Primary outcomes

The primary outcome is the proportion of participants varying to one IPAQ class at least (low-moderate or high or moderate-high) at 3 months [28]. The IPAQ short form (International Physical Activity Questionnaire) is a self-administered questionnaire which measures the physical activity level of people in a heterogeneous population as well as knee osteoarthritis people [31].

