#### Secondary outcomes

● The arthritis self-efficacy influence on pain, function and other symptoms is assessed with the Arthritis Self-Efficacy Scale (ASES) [32] validation in French language is in progress NCT: 02977325 [33].

● Fears and beliefs changes are measured by the Knee OA Fears and Beliefs Questionnaire (KOFBeQ) [34].

● Physical function is assessed by the Western and McMaster Universities Osteoarthritis Index (WOMAC subscale for physical function (W-TPFS)) [35, 36].

● Pain intensity during the last 24 h and the worst pain intensity during the last month are measured by a numerical pain scale.

● Overall psychological status is assessed by the Hospital Anxiety and Depression Scale (HAD) [37, 38].

● The barriers to and facilitators of regular PA practice are assessed by 24 independent and specific items designed by a qualitative study [39], specifically for this study because of no reference scale. Each item will be coded from 0 (strongly disagree) to 4 (strongly agree). The prospective validation of this new scale is in progress.

● Use of pharmacological treatment is recorded (paracetamol, opioids, NSAIDs, intra-articular corticoid/hyaluronic acid).

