#### Statistical analysis

Statistical analyses will be conducted using SAS software (version 9.3.). A two-sided *p*-value of less than 0.05 will be considered to indicate statistical significance (except interim analysis).

Concerning the primary outcome, the comparison between groups will be analysed using Chi-squared or Fisher’s exact tests. Intention to treat (ITT) analysis will be considered for the primary outcome. Then, the analysis of the primary outcome will be completed by multivariate analysis using a generalized linear mixed model (logistic for dichotomous dependent endpoint) to take into account: (1) fixed effects covariates determined according to univariate results and to clinical relevance (for example gender, age and analgesic treatments), and (2) centre as random-effects (to measure between and within centre variability). Continuous endpoints will be compared between groups using Student’s t-test or Mann-Whitney’s test. Normality will be studied by the Shapiro-Wilk test and homoscedasticity using the Fisher-Snedecor test. As suggested by Vickers and Altman [40], the comparison between groups will be completed by linear mixed model considering randomization group and baseline values as independent parameters (fixed effects). Other categorical parameters will be analysed as described previously. Longitudinal analyses concerning repeated measures (for example ASES, KOFBeQ, WOMAC, EVA pain, fears and beliefs, assessed at baseline, after intervention and 3 months after intervention) will be studied using random-effect models (linear or generalized linear), to take into account patient as random-effect (slope and intercept), nestled in centre random-effect, while studying the fixed effects group, time and group *interaction x time*.

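### The supplementary adjusted model for the primary outcome selects covariates partly from univariate results, does not name baseline IPAQ class, and gives analgesic treatment without a time point

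*Protocol article*

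**What the plan says.** All references are to the protocol article.

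- **Primary test (Statistical analysis).** For the primary outcome, "the comparison between groups will be analysed using Chi-squared or Fisher’s exact tests", under intention to treat.
- **Adjusted model (same section).** Next, "the analysis of the primary outcome will be completed by multivariate analysis using a generalized linear mixed model", with centre as a random effect and with "fixed effects covariates determined according to univariate results and to clinical relevance (for example gender, age and analgesic treatments".
- **Baseline adjustment (same section).** It is written out only where continuous endpoints are discussed, as a "linear mixed model considering randomization group and baseline values as independent parameters (fixed effects".
- **Endpoint (Primary outcomes).** It is the "proportion of participants varying to one IPAQ class at least (low-moderate or high or moderate-high) at 3 months". The Exclusion criteria remove people in the high IPAQ class, so everyone starts low or moderate.
- **Drug use.** The section on spa therapy treatment leaves usual and pharmacological care unrestricted in both arms and adds: "Medication taken during or after the intervention will be reported in the follow-up questionnaires". The Secondary outcomes section lists it: "Use of pharmacological treatment is recorded (paracetamol, opioids, NSAIDs, intra-articular corticoid/hyaluronic acid". The Time-point outcomes section places study outcomes at baseline, at 18 days and at 3 months.
- **Allocation (Randomisation).** It is by alternate month within centre. The Discussion accepts that the quasi-randomised method could be a limitation.

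**The concern.** The adjusted model is the only covariate-adjusted arm comparison that the article describes for the primary outcome. In an alternate-month design it is what a reader will turn to when asking whether the arms were comparable. Three features weaken it for that purpose.

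1. Choosing covariates by their univariate results makes the adjusted estimate depend on the data that it analyses, and leaves room for choice after the results are seen. This is a stated rule, so an analysis plan that followed it would carry it forward.
2. The binary endpoint is change relative to baseline class. A low participant responds by reaching moderate or high, a moderate participant only by reaching high. Baseline class is therefore the natural first covariate, yet it is not named.
3. Analgesic use is offered as a covariate with no time point. If a value from during or after the programme were used, the model would condition on something that the programme may itself change, and could adjust away part of its effect.

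**Working it through.** **Step 1: the plan's own figure.** Inputs (Sample size estimation): 25% vs 5%, two-sided 5%, 80% power, 65 per group. The pooled formula is n = [1.960 × √(2 × 0.15 × 0.85) + z_power × √(0.25 × 0.75 + 0.05 × 0.95)]² / 0.20².

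- 80% power: (0.990 + 0.408)² / 0.04 = 48.8, so 49 per group.
- 90% power: (0.990 + 0.621)² / 0.04 = 64.9, so 65 per group.

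The stated 65 thus matches 90% power by this formula. The plan is not underpowered, and the mismatch does not bear on this point. The rates and group size are used below as stated.

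**Step 2: information available for selection.** Expected responders = 65 × 0.25 + 65 × 0.05 = 16.25 + 3.25 = 19.5. That supports only a few covariates.

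**Step 3: does univariate selection distort the test?** Simulation of ordinary logistic models, without a centre effect: 65 per arm, 1,500 runs, half of participants starting low, assumed control response of 25% (low) and 5% (moderate), candidates being baseline class plus 8 pure-noise covariates, entry at p < 0.2. The entry level and candidate list are assumptions, as the article gives neither.

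| Model | Rejection, no effect | Power, log odds ratio 1.5 |
|---|---|---|
| Unadjusted | 4.0% | 88.5% |
| Univariate selection | 3.9% | 91.4% |
| Baseline class pre-specified | 4.0% | 92.1% |

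Selection among noise covariates did not inflate the type I error. In the no-effect runs the selected model had a median of 5.5 responders per fitted term (arm plus covariates), which is thin. Selection from a treatment-affected covariate was not simulated.

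**Step 4: what imbalance in baseline class could do.** With no treatment effect, arm difference = (p_low − p_mod) × (difference between arms in the share starting low). The documents give no class-specific rates and no class distribution, so every input here is assumed. Rejection rates are for the unadjusted two-sided 5% test, 65 per arm, average share low 50%.

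| p_low, p_mod | Imbalance | Spurious difference | Rejection |
|---|---|---|---|
| 20%, 10% | 10 points | 0.10 × 0.10 = 1 point | 5.3% |
| 20%, 10% | 20 points | 0.10 × 0.20 = 2 points | 6.2% |
| 25%, 5% | 10 points | 0.20 × 0.10 = 2 points | 6.2% |
| 25%, 5% | 20 points | 0.20 × 0.20 = 4 points | 9.7% |
| 30%, 10% | 15 points | 0.20 × 0.15 = 3 points | not computed |
| 40%, 10% | 20 points | 0.30 × 0.20 = 6 points | not computed |

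This shift falls on the unadjusted comparison. A model containing baseline class is the means of correcting it.

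**Step 5: when is analgesic use measured?** The sections do not settle it. The one sentence specific to medication concerns use during or after the intervention. The baseline list under Measures does not name analgesics. Drug use is, however, a listed secondary outcome, and study outcomes are also collected at baseline. A pre-treatment value is therefore probably available, but nothing says that it is the value that enters the model.

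**The case against.** The case for leaving the text alone is substantial.

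- **The model is supplementary.** The primary test is unadjusted, so covariate selection cannot alter the primary result. This stands and limits the weight of the point.
- **Baseline class is not excluded.** The named covariates are only examples, and clinical relevance could admit baseline class. If class is strongly prognostic, univariate screening would probably pick it up. A reader might infer that the plan leaves class out; the text supports only that it is not named or pre-specified. But entry would then depend on the screening result, whereas a covariate built into the endpoint should not.
- **Analgesic use may be a baseline value.** A reader might infer from the medication sentence that drug use is recorded only during or after treatment. The Time-point outcomes section contradicts that. The Measures list proves little by silence, since it does not name gender or IPAQ either. What stands is that the time point is unspecified.
- **Both eligible classes can respond.** It would be too strong to say that baseline class decides who can respond. It sets which transition counts, and probably how likely it is.
- **An article may leave the covariate list to a fuller document.** That is fair for the list itself, but not for a stated selection rule that the fuller document would inherit.

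**Conclusion.** The point holds as a weakness of the supplementary adjusted analysis. Its covariates are partly data-driven with about 20 expected responders, it does not name the baseline class against which response is defined, and it leaves the timing of analgesic use open.

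The demonstrated harm is loss of pre-specification. The simulation showed no type I inflation from univariate selection and only a small power difference from the pre-specified model (91.4% vs 92.1%). The possible bias from baseline-class imbalance was 1 to 6 points in the cases tried, against a target of 20, and rests wholly on assumed response rates and imbalances. Adjustment for a treatment-affected covariate would arise only if a post-baseline analgesic value were used, which the article neither states nor rules out. Nothing here shows that the primary conclusion would be wrong. This is a free improvement.

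**What to change.** In Statistical analysis:

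1. Remove univariate results as a criterion for choosing covariates.
2. Pre-specify the adjusted model for the primary outcome as arm and baseline IPAQ class (low or moderate) as fixed effects, with centre as the random effect already stated. Keep age and sex, at most, for a sensitivity model, given about 20 expected responders.
3. State that analgesic treatment may serve as a covariate only as its pre-treatment value. Otherwise analyse it only as the secondary outcome that it already is.

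The cost is analysis wording only. Baseline IPAQ class is already determined to apply the exclusion of the high class, so no new data, visits or participants are needed.

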### Statistical considerations

#### Sample size estimation

According to previous works presented in literature [11], we have estimated that a sample size of *n* = 65 patients per randomized group, for a two-sided type I error at 5%, would provide 80% statistical power of detecting an absolute difference of 20% (25% vs 5.) in the primary outcome: proportion of participants varying to one IPAQ class at least (low-moderate or high or moderate-high). Finally, a total of *n* = 142 patients (71 by group) will be considered to take into account lost to follow-up (10%).

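### Continuous secondary endpoints: an unadjusted, apparently pre-test-guided test comes first, and the planned baseline-adjusted model is not named as the deciding analysis

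*Protocol article*

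**What the plan says.** The Statistical analysis section of the protocol article sets out three analyses of continuous endpoints, in this order.

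1. An unadjusted comparison: "Continuous endpoints will be compared between groups using Student’s t-test or Mann-Whitney’s test". The next sentence is "Normality will be studied by the Shapiro-Wilk test and homoscedasticity using the Fisher-Snedecor test". The article does not state outright that these checks select the test, but no other use is given for them.
2. A baseline-adjusted model, introduced with a methods reference: "the comparison between groups will be completed by linear mixed model considering randomization group and baseline values as independent parameters".
3. For scales measured at baseline, after treatment and at 3 months (ASES, KOFBeQ, WOMAC and pain are the examples), a longitudinal analysis. These "will be studied using random-effect models (linear or generalized linear), to take into account patient as random-effect (slope and intercept), nestled in centre random-effect", with group, time and their interaction as fixed effects.

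One threshold is given for all of them: "A two-sided *p*-value of less than 0.05 will be considered to indicate statistical significance". The section does not say which analysis decides if they disagree. Under Randomisation, the arms are formed by alternating months, with stratification by centre.

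**The concern.** The order gives the lead to the weakest of the planned analyses. A comparison of 3-month scores that ignores the baseline score carries part of any baseline difference into the estimated effect, and it leaves explainable variance in the error term. Both matter more than usual here. All patients in an arm come from the same set of months, so balance at baseline is not protected by individual randomisation, and the Discussion itself lists the quasi-randomised method as a possible limitation.

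If the normality and variance checks do choose the test, the quantity estimated also depends on the data. One scale may be reported as a mean difference and another as a rank comparison.

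With several analyses per endpoint at the same 0.05 level and none named as the main one, the unadjusted result could become the reported finding simply because it is listed first.

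**Working it through.** **Inputs from the article.** Two-sided 5% significance, and "a sample size of *n* = 65 patients per randomized group", taken here as the number evaluable at 3 months. That number was derived for the binary primary outcome. The pooled two-sided formula for 25% against 5% gives 49 per group at 80% power and 65 at 90%, so the stated derivation does not reproduce. This is a separate matter and does not affect what follows. The article gives no target effect, SD or sample size for a continuous endpoint, so there is no figure of its own to reproduce on this point.

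**Assumed inputs.** Within-arm SD of 1 at both times; correlation ρ between baseline and 3 months of 0.3 to 0.7; a systematic baseline difference b of 0.2 or 0.3 SD between the arms, carried forward with slope ρ.

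**Standard error of the unadjusted difference.** √(2/65) = 0.175 SD. For scale, 0.2 SD is 0.2/0.175 = 1.14 standard errors. Chance alone under individual randomisation would exceed that about 25% of the time.

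**Power.** The effect giving the unadjusted t-test 80% power is 0.1754 × (1.960 + 0.842) = 0.491 SD. Adjustment multiplies the residual SD by √(1 − ρ²). At ρ = 0.5 the test statistic is centred at 2.802/0.866 = 3.235, so power is Φ(3.235 − 1.960) = 89.9%. The number per arm needed for 80% power becomes 65 × (1 − ρ²), rounded up.

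**Bias and false positives of the unadjusted test of 3-month scores.** The bias is ρb. With no true effect, the rejection rate is Φ(−1.960 + ρb/0.1754) + Φ(−1.960 − ρb/0.1754).

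| ρ | Adjusted power (unadjusted 80%) | n per arm for 80% (unadjusted 65) | Bias, b = 0.2 | False positives, b = 0.2 | False positives, b = 0.3 |
|---|---|---|---|---|---|
| 0.3 | 83.6% | 60 | 0.06 SD | 6.4% | 8.1% |
| 0.5 | 89.9% | 49 | 0.10 SD | 8.8% | 13.7% |
| 0.7 | 97.5% | 34 | 0.14 SD | 12.6% | 22.4% |

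**If the simple test is applied to change scores instead.** The SD of change is √(2 − 2ρ). At the same 0.491 SD effect, power is 65.8%, 80.0% and 95.1% for ρ = 0.3, 0.5 and 0.7, below the adjusted model each time. The bias becomes ρb − b = −(1 − ρ)b, which for b = 0.2 is −0.14, −0.10 and −0.06 SD. It changes sign but does not vanish.

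**Effect of the pre-tests alone.** Trials with 65 per arm and no effect were simulated 6,000 times per setting. The t-test was used only if Shapiro-Wilk in each arm and the variance F-test all passed at 5%, and Mann-Whitney otherwise. The false-positive rate was 5.0% with normal data and 4.8% with skewed (gamma, shape 2) data, so no inflation appeared. In a second simulation (64 per arm, 0.4 SD shift, 3,000 runs per setting) with log-normal skew of sigma 0.35, about 96% of trials were sent to Mann-Whitney.

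**The case against.** A reader might infer that the plan leaves baseline differences uncorrected and wastes power overall. It does neither. The baseline-adjusted model stands in the sentence after the pre-tests, longitudinal models follow, and the power in the table is available to anyone who reads the adjusted result. The costs above belong to the first-step test only.

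The size also depends on inputs that the article does not give. At ρ = 0.3 the gain is under 4 points. Skewed data can narrow it too. In the second simulation, at ρ = 0.5, the pre-test procedure had about 69% to 71% power on skewed data against 75% for the adjusted model; on normal data the gap was 61% against 73%. The share of trials switched to Mann-Whitney reflects the skew that was simulated, and the article says nothing about how its scales are distributed. Pre-testing did not raise the false-positive rate, so no such harm can be claimed.

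It can also be said that ranking the analyses of secondary endpoints is work for a statistical analysis plan, and that a journal article condenses. That would settle the matter if the article were silent. It is not: it states a lead method and gives the better method a supplementary role. Replacing a stated choice with a better one already in the plan is not a request for missing detail.

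What stands is the order and the absence of a deciding analysis.

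**Conclusion.** The point holds in a limited form. For continuous secondary endpoints the lead comparison is unadjusted and apparently guided by pre-tests. It is more exposed to baseline imbalance under alternate-month allocation, and less powerful, than the model that follows it.

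For an assumed 0.2 SD imbalance and correlations of 0.3 to 0.7, the bias on 3-month scores is 0.06 to 0.14 SD and the false-positive rate about 6% to 13%. The power given up is about 4 to 18 points at an effect where the unadjusted test has 80%. The direction does not depend on where in the correlation range the truth lies; the size does.

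The binary primary outcome is not affected. Nor would the adjusted model cure the alternate-month design, although a reader might infer that it would. It corrects for differences in the baseline score, not for season, staffing or other month effects unrelated to that score.

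**What to change.** Name the linear model with group and baseline value, plus centre as the stratification factor, as the main analysis of each continuous endpoint at 3 months. Report the adjusted mean difference with its 95% CI. Delete the use of Shapiro-Wilk and Fisher-Snedecor to select a test and check the model residuals instead. Keep the t-test or Mann-Whitney test as a supportive analysis that does not decide the conclusion, and state the same for the longitudinal model's 3-month contrast.

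This takes one or two sentences. The model is already planned and the baseline values are already collected, so there is no cost in patients, visits or data.

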### Self-management exercise program

The main objective of the self-management exercise program will be to allow people to understand the importance of physical exercise practice and learn when, where and how to practice exercise, in order to adapt their PA practice according to their phenotype and integrate it long term in their daily life.

Each session will consist of 45 min of self-management education and 45 min of PA practice, with aerobic training program, strength training, range of motion and personal feedback. The exercise program will be tailored to each participant. The physiotherapist or adapted PA instructor will drive an experimental arm of 5 to 7 participants. The 5 sessions will take place on days (D) D4, D7, D10, D13 and D16.

For each workshop, a specific objective and operational objectives are defined, linked to criteria and indicators (Table 1).

**Table 1 Tab1:** Self-management education program

Session	Objectives
Session 1: ᅟEvaluate the representation of the patient’s PA	- Identify the representation of PA
	- Identify the barriers to and facilitators of regular PA practice
	-Acquisition of knowledge about OA
	-Know the methods of the exercise practice
Session 2: ᅟDefining the importance of exercise in knee OA	-Name the benefits of PA in the management of knee OA
	-Identify the normal and abnormal physiological signs during the PA practice
	- Learn to adapt the exercise according to its knee OA (intensity, duration)
Session 3: ᅟPatient engagement in regular PA practice	- Determine where, when and how to exercise throughout the year
	- Include an exercise program in everyday life
	- Know the anatomical bases necessary for performing the adapted exercises
Session 4: ᅟThe consequences of stopping the exercise program	-Know the importance of maintaining exercise program on a regular and long-term basis
	-Identify factors that could facilitate or limit the continuation of the exercise program
	-Learn how to build a PA session
Session 5: ᅟKnowledge restitution	- Know the means of managing knee OA
	- Know how to live healthy with knee OA
	-Set an achievable goal

*PA* physical activity, *OA* osteoarthritis

To facilitate the workshops, different teaching tools and techniques will be used: paper board, thematic discussion, participative discussion, practical leaflets (Borg scale, deconditioning circle), information booklet, exercise demonstration, feedback, and pain coping skills.

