### Time-point outcomes

Study outcomes will be collected at baseline and after treatment (18 days) in spa resorts and at 3 months post-randomisation, by mailed self-reporting questionnaires. If needed, the research officer will use a telephone follow-up.

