According to clinical relevance, sub-group analyses depending gender will be proposed after the study of sub-group x randomization group interaction in regression models (for repeated data or not). Secondarily, a per-protocol analysis will be considered. Finally, a sensitivity analysis will be performed and the nature of missing data will be studied (missing at random or not). According to this, the most appropriate approach to the imputation of missing data will be proposed (maximum bias (e.g. last observation carried forward vs. baseline observation carried forward) or estimation proposed by Verbeke and Molenberghs for repeated data). More precisely, concerning the IPAQ score, when participant will mention a number of days, hours or minutes for an activity without checking « yes » or « no » to intense, moderate or walking categories practice, a « yes » response will be imputed to this question. If participant no mentions to the practice of an activity or the number of days, hours or minutes, a « no » response will be imputed to this question.

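### The method for a missing 3-month IPAQ class is chosen after studying whether data are missing at random, and the LOCF/BOCF pair on offer is not a worst-case bound

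*Protocol article*

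**What the plan says.** Under Statistical analysis, after naming the primary tests and intention to treat, the protocol article announces that "a sensitivity analysis will be performed and the nature of missing data will be studied (missing at random or not"). It goes on: "According to this, the most appropriate approach to the imputation of missing data will be proposed". Two kinds of method are then listed: a maximum-bias approach, with LOCF against BOCF as the example ("imputation of missing data will be proposed (maximum bias (e.g. last observation carried forward vs. baseline observation carried forward"), and a published estimation approach for repeated data. A further rule fills blank IPAQ items with yes or no. It deals with incomplete answers, not with a questionnaire that never comes back.

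Time-point outcomes gives the schedule: "Study outcomes will be collected at baseline and after treatment (18 days) in spa resorts and at 3 months post-randomisation, by mailed self-reporting questionnaires", with telephone follow-up if needed. Interventions gives the self-management exercise program to the experimental arm alone. The section on that program states: "The 5 sessions will take place on days (D) D4, D7, D10, D13 and D16", and each session includes 45 minutes of physical activity. Primary outcomes defines the endpoint as the proportion who rise by at least one IPAQ class at 3 months. Sample size estimation assumes 25% against 5%, 71 patients per arm and 10% loss.

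**The concern.** There are two faults.

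- **The selection rule.** Whether data are missing at random depends on the values that were not seen. Observed data can show that missingness is related to recorded variables, but cannot exclude a further dependence on the missing value itself. A method picked on the outcome of that inquiry is picked after seeing the data, on grounds the data cannot supply. An analysis plan that followed this text would inherit the fault.
- **The LOCF option.** Day-18 data are collected in the resort and 3-month data by post, so a patient with the first and without the second is easy to foresee. LOCF would then score the patient on activity reported as the program ends, although the endpoint concerns activity 3 months on. Supervised exercise in that period is given to one arm only.

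At stake is how far the handling of about one patient in ten can move the estimated difference, and whether the pair labelled maximum bias would reveal it.

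**Working it through.** **Inputs from the protocol article.** 71 per arm, 10% loss, 25% against 5% (Sample size estimation); sessions on D4, D7, D10, D13 and D16 (Self-management exercise program); visits at baseline, day 18 and 3 months (Time-point outcomes). The article gives neither day-18 class-change rates nor the IPAQ recall window. Both are treated below as assumptions.

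**Number missing.** 71 × 0.10 = 7.1, so about 7 per arm; 7/71 = 0.0986. Observed share: 64/71 = 0.9014.

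**Which sessions a day-18 IPAQ would cover.** A 3-day recall covers D16 (45 minutes). A 7-day recall covers D13 and D16 (90 minutes). A 5-day recall covers both if it ends the day before day 18, and only D16 if it ends on day 18. A recall shorter than 2 to 3 days covers none.

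**Inflation from LOCF.** Let q be the share of missing experimental patients who had moved up a class at day 18, and p their true 3-month rate. Missing controls are taken to have the same 5% rate at day 18 as at 3 months, so they add no error. Inflation = 0.0986 × (q − p).

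| q | No true effect, p = 5% | Design effect, p = 25% |
|---|---|---|
| q = p | 0 | 0 |
| 50% | 0.0986 × 0.45 = 4.4 points | 0.0986 × 0.25 = 2.5 points |
| 100% | 0.0986 × 0.95 = 9.4 points | 0.0986 × 0.75 = 7.4 points |

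If 25% of missing controls had also moved up at day 18, the no-effect entries fall to 0.0986 × (0.50 − 0.25) = 2.5 and 0.0986 × (1.00 − 0.25) = 7.4 points.

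**False-positive rate.** Exact enumeration of the chi-squared test with 71 per arm, 10% missing and 5% against 5%: BOCF rejects in 4.7%. LOCF rejects in 7.8%, 18.0% and 49.7% for q = 25%, 50% and 100% with 5% of missing controls moved up. With 25% of missing controls moved up, it rejects in 8.6% (q = 50%) and 30.4% (q = 100%).

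**Does the LOCF/BOCF pair bound the bias?** At the design rates with 7 of 71 missing per arm:

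- BOCF (no class change in either arm): 0.9014 × 0.25 = 22.5% against 0.9014 × 0.05 = 4.5%, a difference of 18.0 points.
- LOCF with q = 100%: 22.5% + 9.9% = 32.4% against 5.0%, a difference of 27.4 points.
- Worst case (missing experimental patients fail, missing controls succeed): 22.5% against 4.5% + 9.9% = 14.4%, a difference of about 8 points.

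The pair spans 18.0 to 27.4 points at most. It stops well short of 8.

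**The case against.** The case for the plan is substantial on the LOCF half.

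- **A day-18 IPAQ is not stated.** Primary outcomes mentions only 3 months, Aim links 18 days only to sarcopenia, and the examples of repeated measures under Statistical analysis omit the IPAQ. This stands, so the LOCF point is conditional. But that list is given as examples, and Time-point outcomes makes no exception for the IPAQ. Without a day-18 IPAQ, the LOCF/BOCF contrast is empty for the primary outcome.
- **LOCF is not the primary rule.** A reader might infer that the intention-to-treat result will rest on LOCF. The text does not support that: the passage opens with a sensitivity analysis, LOCF is an example set against BOCF, and a third method is named. What remains is that no other text covers an absent 3-month IPAQ.
- **The label belongs to the contrast.** Maximum bias describes the pair, not LOCF alone, and the pair can be read as a bracket. Agreed, but the bracket lacks the side that matters, as the 8-point case shows.
- **Both arms are active at the spa.** Both have 18 sessions with supervised pool mobilisation, so controls' day-18 activity may rise too. This narrows the gap. The article also does not show that 45 to 90 minutes would change a class.
- **Earlier sessions.** One might count D10 as well, but that needs a recall longer than 7 days, and no window is given.
- **Detail belongs to the analysis plan.** True of the mechanics of imputation. But the article does more than leave a gap: it states a data-driven rule.

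**Conclusion.** The selection rule is unsound as written: it makes the missing-data method depend on a finding that observed data cannot provide. This part needs no assumption.

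The LOCF part holds conditionally. If the IPAQ is collected at day 18, carrying it forward probably favours the experimental arm; if not, LOCF and BOCF are the same analysis of the primary outcome. Either way, neither analysis treats missing experimental patients less favourably than missing controls, so the pair is not a maximum-bias bound.

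The size is not known. The ranges of 0 to about 9.4 points (no true effect) and 0 to about 7.4 points (true experimental rate 25%) assume 7 of 71 missing per arm, a day-18 value for each of them, a day-18 rate no lower than the 3-month rate, and no rise in controls. They show what is possible beside a 20-point target; they do not predict the bias. This should be corrected before analysis, but it does not show that the planned primary result is biased.

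**What to change.** 1. Delete the step that decides from the data whether they are missing at random. State missing at random as an assumption where a method needs it.
2. Prespecify one handling of a missing 3-month IPAQ class for the intention-to-treat analysis. Either multiple imputation by arm under missing at random, or missing = no class change in both arms, would serve. If a day-18 IPAQ exists, it may be a predictor in the imputation model; it should not be carried forward. With only about 0.05 × 64 = 3 class changes expected among observed controls, such a model must be small.
3. Replace LOCF from day 18 with prespecified sensitivity analyses: missing = no class change (if not already primary), plus a tipping-point or worst-case analysis against the experimental arm.
4. State whether the IPAQ is collected at day 18.

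The cost is wording and modest programming. The estimated effect may be slightly smaller: missing = no class change would give 18.0 instead of 20 points at the design rates.
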